## Abstract

**Introduction:**

Children with congenital heart disease (CHD) are at risk for executive functions (EF) impairments. To date, interventions have limited effects on EF in children and adolescents with complex CHD. Therefore, we developed a new multimodal and personalised EF intervention (E-Fit). This study aims to test the feasibility of this intervention called ‘E-Fit’ for children with complex CHD and EF impairments.

**Methods and analysis:**

This is a single-centre, single-blinded, randomised controlled feasibility study exploring the E-Fit intervention. We aim to enrol 40 children with CHD aged 10–12 years who underwent infant cardiopulmonary bypass surgery and show clinically relevant EF impairments (T-score ≥60 on any Behaviour Rating Inventory for Executive Function questionnaire summary scale). The multimodal intervention was developed with focus groups and the Delphi method involving children and adolescents with CHD, their parents and teachers, and health professionals. The intervention is composed of three elements: computer-based EF training using CogniFit Inc 2022, performed three times a week at home; weekly EF remote strategy coaching and analogue games. The content of the computer and strategy training is personalised to the child’s EF difficulties. The control group follows their daily routines as before and completes a diary about their everyday activities four times a week. Participants will be randomised in a 1:1 ratio. Feasibility is measured by the participants’ and providers’ ratings of the participants’ adherence and exposure to the intervention, recruitment rates and the evaluation of the intended effects of the programme.

**Ethics and dissemination:**

Local ethics committee approval was obtained for the study (BASEC-Nr: 2021-02413). Parents provide written informed consent. Key outputs from the trial will be disseminated through presentations at conferences, peer-reviewed publications and directly to participating families. Furthermore, these results will inform the decision whether to proceed to a randomised controlled trial to investigate effectiveness.

**Trial registration number:**

NCT05198583.

STRENGTHS AND LIMITATIONS OF THIS STUDYThe intervention was designed based on extensive input from patients with congenital heart disease, families, teachers and health professionals provided through focus group interviews and the Delphi method.Using a multiple-domain approach, the intervention will be personalised towards individual patients’ and families’ needs.Assessors are blinded to the group allocation of participants.Families of the control group may be aware of the content of the intervention and engage in its activities, which might reduce the effect sizes of the intervention.Considering the limited sample size of this feasibility study, the effectiveness of the training will only be estimated exploratorily.

## Introduction

Eight out of 1000 children are born with congenital heart disease (CHD)^1^; of these, one-third require open heart surgery during infancy.^2^ In these children, neurodevelopmental problems are known to be a main comorbidity.^3^ Studies have shown that the mean IQ of children with CHD is within the normal range but lower than that of their healthy peers.^4^ Despite this normal intellectual functioning, children with complex CHD, particularly, are at risk for higher-order cognitive deficits: executive function (EF) impairments.^4 5^ The main EF are inhibition; cognitive flexibility, including fluency; planning and working memory.^6–10^ Children with CHD show mild to moderate impairments in all these EF domains^4 5^ without a clear predominance of any specific EF domain. In typically developing children, EF are more closely related to school readiness than IQ, and EF predict academic achievement.^11^ Accordingly, EF difficulties in childhood have been related to higher unemployment rates in adulthood.^12^ Further, EF difficulties in adulthood can increase the risk of addictive behaviours and psychiatric diseases such as anxiety and depression.^13 14^

Many sequelae of EF difficulties have also been demonstrated in children with CHD. They face lower school achievement and lower psychosocial quality of life (QoL) during school age.^15 16^ Further, lower EF have been associated with a higher rate of internalising symptoms in adolescents and adults with CHD.^17^ Given the lifelong academic, psychological and social burden associated with EF difficulties, evidence-based interventions improving EF are urgently needed, particularly for children and adolescents with CHD.^18 19^

### EF intervention

To date, only two studies have investigated the efficacy of EF interventions in children with CHD.^20^
^21^ Both studies included school-aged children and adolescents with CHD and tested Cogmed Working Memory Training (Cogmed^22^). Cogmed is a computerised programme designed to improve attention and working memory, a core dimension of EF.^22^ Participants completed regular Cogmed sessions at home for at least 5 weeks.^20 21^ These studies demonstrated inconsistent findings: Calderon *et al* found no improvement of working memory either at postintervention or at 3-month follow-up, but participants who did the Cogmed sessions showed significant improvements in inhibitory control and self-regulation at the 3-month follow-up. Parents reported improved cognitive regulatory skills at postintervention and 3-month follow-up.^21^

In contrast, Jordan *et al* found improved working memory postintervention in participants who were assigned to Cogmed compared with the control group. However, this improvement did not persist longer than 6 months follow-up.^20^ These findings are in line with the inconsistent results of a recent meta-analysis of EF interventions in other children at risk for EF impairments.^23^ This meta-analysis reported only small to moderate effects of computerised interventions of single functions and no evidence for long-term effects. These inconsistencies between EF interventions have led to investigations about factors impacting the effectiveness of an EF intervention.^23^ One of those factors is motivation, which influences the effort a participant is willing to make, which further impacts the intervention’s success.^24^ Game elements are able to increase motivation, and therefore, using computerised interventions with game elements is a favourable option.^25^ Also, analogue games, such as board and card games, have been tested as EF interventions and have shown effectiveness in enhancing the functions trained.^26 27^ Moreover, by requiring children to play with others, such games may enhance self-monitoring.^26^ Studies combining computer and analogue games demonstrated improvements in trained reasoning and speed tasks in healthy children with low socioeconomic status (SES) aged 7–10 years.^27^ However, despite the enjoyment factor, a major challenge in interventional studies is the limited transfer of training effects to other cognitive abilities.^28–31^ Importantly, a meta-analysis revealed that programmes emphasising teaching social-emotional strategies and self-regulation had the most significant positive impact on EF, particularly for children with neurodevelopmental disorders or behavioural problems. These effects appeared to be stronger than those observed in trainings primarily focusing on tasks specifically training EF and may address the transfer of training to general cognitive abilities.^18 28 32^ Therefore, exploring intervention approaches beyond computerised and tasks-specific training is crucial.^18^ Mindfulness education has improved EF behaviour, optimism and classroom social competence behaviours in healthy children and adolescents.^33 34^ Similarly, problem solving solutions to EF-related challenges in everyday life improved parent-rated and self-rated global EF behaviours in children with epilepsy.^32^ Hence, mindfulness interventions and strategy coaching may address the transfer of training to everyday life by targeting sensory awareness and attention regulation, thus promoting emotional and social development.^18 32–34^

Combining established and engaging computerised and analogue training that improves individual EF, alongside strategy coaching aiming at integrating these benefits into daily life, presents a promising approach for addressing the aforementioned limitations of current interventions.

Because children with CHD experience difficulties in various EF domains with significant academic, psychological and social consequences, an intervention integrating several of these approaches may be particularly suited to improving these children’s EF and, eventually, their long-term development and social integration.

### Aims and hypotheses

This study aims to test the feasibility of a multimodal personalised EF intervention for children with complex CHD and EF impairments. To evaluate E-Fit’s feasibility, the following aims and hypotheses will be explored:

Aim 1: Assess whether children with CHD and EF impairments can adhere to E-Fit.

Hypothesis 1: Study participants will complete at least 80% of the strategy coaching and computerised training sessions of E-Fit.

Aim 2: Assess the acceptability of E-Fit for children with CHD and EF impairments and their parents.

Hypothesis 2: Study participants and their parents will indicate high acceptability of E-Fit as measured by average ratings of 3 or higher on a 4-point rating scale assessing the acceptability of each programme component.

Aim 3: Assess the feasibility of E-Fit for children with CHD and EF impairments and their parents.

Hypothesis 3: Study participants and their parents will indicate high feasibility of E-Fit as measured by average ratings of 3 or higher on a 4-point rating scale assessing the user-friendliness and ease of integrating each programme component into their daily lives and environments.

Aim 4 (exploratory): Measure the impact of E-Fit on improving EF skills in children with CHD and EF impairments.

Hypothesis 4: We anticipate a moderate effect in the direction of improved EF from preintervention to postintervention in study participants.

The rationale for projection numbers provided in the hypotheses is as follows:

Adherence of 80% is based on previous intervention studies.^21^

The decision to use rating scale ratings of 3 or higher is founded on the 4-point rating scale (1=do not agree at all, 4=fully agree). Therefore, 3 and above are considered affirmative.

Effect sizes are based on the results of a meta-analysis. Specifically, a value of 0.38 pertains to explicit EF practice (including computerised and analogue training across all populations), while 0.46 corresponds to strategy coaching across all populations.^23^

## Methods and analysis

In this section, we will first describe the development of the intervention, which involved a needs assessment preceding the present investigation. Subsequently, we will outline the methods used in the present feasibility study. For an overview, see figure 1.

**Figure 1 F1:**
[figure not shown]
Flow chart of intervention development and trial design. *from baseline. BRIEF, Behaviour Rating Inventory of Executive Functions; CHD, congenital heart disease; EF, executive function; E-Fit, EF intervention.

### Needs assessment

Before developing E-Fit and this study, we conducted a needs assessment. This assessment aimed to specifically identify the unique EF needs of children with CHD by means of focus group interviews and the Delphi method. Below, you will find comprehensive details about the focus group interviews and the Delphi method, including the outcomes that led to the final intervention.

#### Focus group interviews

We conducted two separate online focus group interviews: one with five adolescents with CHD aged 14–16 years and another with seven of their parents (n_female_=5). Participants were recruited from the Teen Heart Study, which investigated EF in children and adolescents with CHD at the University Children’s Hospital Zurich. The Teen Heart Study included children and adolescents with CHD without genetic or dysmorphic syndromes who were born between 2004 and 2012 and underwent their first cardiopulmonary bypass (CPB) surgery before the age of 6 years.^35^ Participants were asked what they consider the ideal content and scope of an intervention supporting EF in children with CHD (eg, (1) how much time can or should your child invest per (a) week, (b) per day, (c) how long in total? (2) Which difficulties does your child have in everyday life?; see online supplemental file 1). These interviews were recorded with the consent of the participants and then transcribed and analysed with structured qualitative content analysis.^36^ This analysis produced nine categories, and all participants’ suggestions and statements were assigned to one of these categories (online supplemental table S1).

10.1136/bmjopen-2023-073345.supp1Supplementary data

10.1136/bmjopen-2023-073345.supp7Supplementary data

#### Delphi method

The results from the focus group interviews informed the initiation of the Delphi method, aiming to achieve consensus on the intervention’s content through three sequential questionnaires.^37^ During this procedure, the items of a survey are rated and evaluated multiple times, each time anonymously. The participants subsequently receive the next survey, along with feedback on the overall answers.^38 39^

The surveys were completed online by children with CHD (n=7) aged 12–13 years who had not participated in the preceding focus group interviews, their teachers (n=5), parents (n=7) and health professionals (n=5). The health professionals were experts in the field from international hospitals and research institutions who held a comprehensive understanding of the difficulties faced by children with CHD. They had previously engaged with the research group and were contacted by email. The families were again recruited from the Teen Heart Study, but following focus group interview suggestions, only participants between 10 and 13 years old were asked to participate. The families provided the email addresses of the teachers to be contacted by the study team. Hence, the surveys were completed by four stakeholder groups: children with CHD, parents of children with CHD, teachers of children with CHD, and health professionals.

For survey 1, respondents received a link by email and were invited to rate each item on a Likert scale from 1 for ‘fully disagree’ to 9 for ‘fully agree’. They were encouraged to make further suggestions yet to be represented in the survey. Survey 2 was sent to all respondents of survey 1. All items from survey 1 were included, and additional items suggested by participants were added following revision and categorisation. The results of survey 1 were included in survey 2: A table displayed the median and IQR per stakeholder group for each item, and each participant was reminded of the scores they had given in survey 1. Participants were asked to consider the input of all stakeholder groups in survey 1 and then review their answers. Items reaching consensus (IQR<2) were dropped from the subsequent round. Survey 3 was sent to all respondents of survey 2. Items for which no consensus was reached in survey 2 were included. No more items were added. Again, the results of survey 2 were included in survey 3. Participants again reviewed their answers. At the end of survey 3, every participant was asked about their interest in participating in the final consensus meeting. Throughout the process, all stakeholder groups responded to the same items.

Overall, participants completed three rounds with the goal of consensus-seeking across stakeholder groups, defined as IQR<2 for each item.^40^ Items for which no consensus was reached after three rounds were discussed in a final consensus meeting with three parents, two health professionals and the study team. In the consensus meeting, it became clear that some aspects of the intervention are child-specific and cannot be answered conclusively. To families, it was particularly important to have a diverse intervention that was not too school-like. The researchers commented on the intervention in terms of methodological aspects, which were taken into account in the study design (eg, additional questionnaires or incentives to be added).

#### Findings from needs assessment

The results of the Delphi method, including the consensus meeting, showed that the wishes most strongly expressed by parents were that the intervention should include strategies supporting homework and everyday life activities and that the children should learn to develop their own strategies. Families participating in the Delphi method wanted activities that did not resemble schoolwork, improved reasoning skills, and addressed academic future planning (online supplemental figure S1). Parents emphasised that the ideal age at which an EF intervention should start depends on the individual child, ranging from 4 to 18. Literature shows that EF development progresses considerably during childhood and adolescence.^18^ This opens a window of opportunity for EF training during these periods.^41 42^ Also, the families’ perceived need for therapy is crucial for adherence.^43^ During school age and adolescence, families become more aware of the sequelae of CHD and thus become more willing to participate in an intervention programme. Participants also wanted minimal parental participation in the intervention, and the focus group interviews indicated that participants became aware of EF problems shortly before high school when remedial action might still be effective.

Consequently, we decided on an age range of 10–12 years instead of younger or older. No consensus was reached on whether the intervention should include personal meetings with the study team, whether the intervention should occur in a nearby community centre, or on the design of the games (online supplemental figure S1). The consensus meeting indicated that responses on these topics differed between children and families, and general agreement was difficult to reach. Hence, literature and practice in previous programmes were used to decide on these elements.^18 20 21 43–48^ For details, see online supplemental file 2 and supplemental material online supplemental figure S2.

10.1136/bmjopen-2023-073345.supp2Supplementary data

### Study design to test the feasibility of the intervention

This is a single-centre, single-blinded, randomised controlled feasibility study to test the feasibility of the E-Fit intervention.

All participants undergo a baseline neurodevelopmental assessment (table 1) and are randomly assigned to either the E-Fit intervention or to the control group. All participants undergo a 2-month postintervention and a 6-month follow-up assessment. Investigators administering neuropsychological tests are blinded to the participant’s allocation. The families and the psychologist who conducts the intervention are aware of the allocation (online supplemental table S2).

**Table 1 T1:** Executive function domains

EF domain	Assessment test
Inhibition	Colour Word Interference Task (D-KEFS^70^) Go/No-Go (TAP^71^)
Cognitive flexibility	Trail-making Test (D-KEFS^70^) Colour Word Interference Task (D-KEFS^70^)
Planning	Tower Test (D-KEFS^70^)
Working memory	Digit Span (WISC-V^66^) Picture Span (WISC-V^66^) No Letter Sequencing (WISC-V^66^)
Risk-taking	Balloon Analogue Risk Task^72^

D-KEFS, Delis-Kaplan Executive Function System; EF, executive function; WISC-V, Wechsler Intelligence Scale for Children fifth edition.

### Participants and recruitment

This study includes children with CHD who underwent CPB in Switzerland before 1 year of age. Diagnoses may include transposition of the great arteries, hypoplastic left heart syndrome and other complex CHDs requiring CPB. At recruitment, children are 10–12 years old. Children diagnosed with a genetic or dysmorphic syndrome such as trisomy-21 or Ellis-van Creveld syndrome or with known large cerebral lesions or injuries, including stroke and severe hypoxic-ischaemic encephalopathy with significant neurological sequelae preventing them from performing the assessments are excluded.

Recruitment for the study commenced in April 2022 and is planned to continue until fall 2023. Children from the Department of Cardiology outpatient clinic at the University Children’s Hospital Zurich are being contacted consecutively. Follow-up assessments are scheduled to be completed by the beginning of 2024. Participants are identified through the clinical database comprising all treated children with CHD. All eligible children with CHD and their parents receive a letter with the study information and are asked to contact the study team if they are interested in participating. The study team provides further information about the study and answers questions on the phone. The contact information of the children’s teachers is forwarded by the parents, and after agreeing to participate and giving written informed consent (online supplemental file 3), parents and the child’s principal teacher fill in the Behaviour Rating Inventory of Executive Functions (BRIEF^49^) screening questionnaire. The BRIEF assesses EF behaviours in children and adolescents on three summary scales: a Behaviour Regulation Index, a Metacognition Index and a Global Executive Composite. Participants are included in the study if a T-score≥60 on any of the three summary scales is reported by either parents or teachers.

10.1136/bmjopen-2023-073345.supp3Supplementary data

### Randomisation and stratification

After passing the screening questionnaire, participants will be randomly assigned to either the intervention or control group in a 1:1 design by block randomisation (block size=4, stratification variable: maternal education level on a 6-point Likert scale). This list of random numbers will be generated prior to the start of the study in the statistical software R^50^ and implemented in the randomisation module on the research electronic database Redcap,^51^ which allows allocation to be concealed until the participant is enrolled. At the end of the first assessment, after all tests and questionnaires are completed, the child will open an envelope prepared by a study member otherwise not involved in the study. The note in the envelope will reveal the allocation status to the family and baseline assessor.

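### The baseline assessor is told each child's allocation, yet the blinding statements make no exception, and the article never says that someone else tests the child at 2 and 6 months

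*Protocol article*

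**What the plan says.** Three places in the protocol article bear on who knows the allocation.

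- **Study design section.** "Investigators administering neuropsychological tests are blinded to the participant’s allocation". The next sentence names those who are not blinded: "The families and the psychologist who conducts the intervention are aware of the allocation", with a reference to online supplemental table S2. The baseline assessor is not named. On later visits the section says: "All participants undergo a 2-month postintervention and a 6-month follow-up assessment".
- **Strengths and limitations box.** "Assessors are blinded to the group allocation of participants". No visit or person is excepted.
- **Randomisation and stratification.** "At the end of the first assessment, after all tests and questionnaires are completed, the child will open an envelope", and then: "The note in the envelope will reveal the allocation status to the family and baseline assessor". The list is built with "block size=4, stratification variable: maternal education level on a 6-point Likert scale".

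Table 3 places the D-KEFS, the WISC-V, the Test of Attentional Performance and the Balloon Analogue Risk Task at baseline, T1 and T2 in both groups, under limited efficacy. The BRIEF has the same schedule but is completed by parents and teachers.

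**The concern.** Someone who gives the baseline neuropsychological tests is, by the described procedure, told the child's allocation. The two general statements on blinding leave no room for such a person, and the list of aware persons omits them. Read together, the sections do not tell the reader whether the tests that follow the reveal are masked.

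This matters because assessor masking is the only masking the article claims. Families and coaches know the allocation, so the single-blind label rests on the people who give the tests. Limited efficacy is one of the six areas under primary outcome measures, the benchmark effects given under aims and hypotheses are modest (0.38 and 0.46), and the pilot data are to inform whether a definitive trial goes ahead. If an examiner who knew the allocation gave the follow-up tests, a between-group difference of that order could not be cleanly separated from examiner influence. The article offers no basis for putting a size on such influence.

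The same disclosure has a second effect. A person told each result in turn, under a fixed and published block size, can sometimes work out what the next child in the stratum will receive before testing that child at baseline.

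**Working it through.** **1. Blinding at each visit.** No arithmetic applies, so the statements are set against the order of events.

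| Testing | Relation to the reveal | Is the tester masked to this child's allocation? |
|---|---|---|
| Baseline | Before it: the envelope is opened once all tests and questionnaires are done | Yes, as far as disclosure goes (prediction is taken up in step 2) |
| 2 months (T1) | After it | Only if the tester is not this child's baseline assessor |
| 6 months (T2) | After it | Only if the tester is not this child's baseline assessor |

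The text available does not say who tests at T1 and T2. The unqualified blinding statements are true of T1 and T2 under one staffing arrangement and false under another, and the article does not state which applies. Under either arrangement, the list of aware persons in the study design section is incomplete, because it omits the baseline assessor.

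**2. Predictability in blocks of 4.** Inputs: block size 4, 1:1 ratio and six maternal education levels (randomisation section); 40 children (sample size section). Assumption: one assessor sees every allocation in a stratum in order, and knows the block size and the mother's education level.

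A block has six equally likely sequences: AABB, ABAB, ABBA and their mirror images.

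- *Allocations fully determined by earlier ones.* AABB has 2 (third and fourth), ABAB has 1 and ABBA has 1; the mirrors are the same. Mean = 2 × (2 + 1 + 1)/6 = 8/6 per block. Share = (8/6)/4 = **33%**.
- *Best-guess rate.* The chance of a correct guess is 1/2 at position 1, 2/3 at position 2, (1/3 × 1) + (2/3 × 1/2) = 2/3 at position 3, and 1 at position 4. Sum = 17/6 per block. Rate = (17/6)/4 = **70.8%**, against 50% with no information.

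These are complete-block figures. If 40 children spread evenly over six strata, each stratum holds 40/6 = 6.7 children, that is 6 or 7: one full block and part of a second.

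- *Stratum of 6.* Determined: (4/3 + 0)/6 = **22%**. Best guess: (17/6 + 1/2 + 2/3)/6 = 4/6 = **67%**.
- *Stratum of 7.* Determined: (4/3 + 1/3)/7 = (5/3)/7 = **24%**. Best guess: (4 + 2/3)/7 = **67%**.

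The actual stratum sizes are not given. If several assessors share the baseline visits and do not exchange results, each can predict less.

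**The case against.** The strongest reply is that the passages can all be true. The term baseline assessor is specific to one visit and may imply that a different person tests at follow-up. The general blinding statement, applied to T1 and T2, would itself exclude anyone who has seen the note. Supplemental table S2 is cited exactly where the article says who is aware, and a condensed article may leave staffing by visit to such a source.

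Much of this stands. A reader might infer that the trial contradicts itself outright, or that follow-up testing is unblinded. The documents do not support either inference: no sentence says that the same person tests at 2 or 6 months. Nor do they support the inference that baseline scores are collected with the child's allocation disclosed, because the reveal comes after all baseline tests.

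The reply does not remove the point. The article makes an unqualified claim and then describes a procedure that makes one tester an exception. Even if table S2 assigns follow-up to someone else, the blinding statements and the list of aware persons still need that exception written in.

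On predictability, it is fair to say that 33% and 71% are upper figures for complete blocks and a fully informed assessor. Consent and BRIEF screening also precede the baseline visit, so a guess made there cannot change whether the child passed screening. What remains is possible influence on baseline testing, of unknown size. It is a secondary matter.

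The reach is also limited. Assessor masking does not protect the BRIEF, which parents and teachers complete, and the efficacy aim is declared exploratory.

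**Conclusion.** The point holds as a gap between the blinding claim and the described procedure. Each child's baseline assessor learns the allocation after that child's baseline tests. The article does not state that this person is kept from testing the child at T1 or T2. The masking of the examiner-administered EF tests at 2 and 6 months is therefore claimed but not secured by the text available, subject to table S2.

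Any bias in test scores cannot be sized from the documents. The predictability figures are an upper bound of 33% determined and 71% best guess, falling to about 22–24% and 67% under an even spread of 40 children over six strata. All of them assume one assessor who sees every allocation in order.

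The consequence is confined to the exploratory limited-efficacy tests. Adherence, acceptability and feasibility ratings are not affected, and neither is the BRIEF.

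**What to change.** 1. Have the envelope opened without the assessor in the room, by the family alone or with the independent study member who prepared it. In the randomisation section, name only the family as those to whom the note reveals the allocation. The coach is a poor choice for this step, because coaching is remote and control families have no coach.
2. State that nobody who knows a child's allocation tests that child at T1 or T2.
3. Reconcile the strengths and limitations box, the study design section (including its list of aware persons) and the randomisation section, and check them against supplemental table S2.
4. For children already enrolled, report whether the baseline assessor also gave the 2- or 6-month tests.

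The first step also withholds the running results that make block prediction possible, so the block size need not change on this account. The cost is a minor change to the end of the baseline visit and a few sentences of text. If a different person already tests at follow-up, T1 and T2 masking needs only the wording.
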